#### Secondary Outcome Measures

A range of secondary measures will be explored as outlined below.

**Table 1 table1:** Nutritional composition of study feeds. RE: retinol equivalent. α-TE: alpha tocopherol equivalent. NE: niacin equivalent.

Formula Composition		Nutrison Protein Plus Multifibre (per 1000mL/per kcal/1000mL)	Glucerna Select (per 1000mL)	Diason (per 1000mL)
Energy (kJ)		5350/4180	4170	4350
Protein (g)		63/49 (20%E^a^)	50 (20%E^a^)	43 (17%E^a^)
Carbohydrate (g)		141/110 (44%E^a^)	75 (28.6%E^a^)	113 (44%E^a^)
Fat (g)		49/38 (34%E^a^)	54 (48%E^a^)	42 (36%E^a^)
Saturated Fat(g)		13/10.2	4	5
Monounsaturated Fat(g)		27/21	Not specified	30
Polyunsaturated Fat(g)		9/7	Not specified	7
Fiber (g)		15/12	21	15
**Micronutrients (Minerals and Vitamins)**				
	Sodium (mg)	1110/867	940	1000
	Potassium (mg)	1680/1313	1300	1500
	Calcium (mg)	900/703	700	800
	Phosphorus (mg)	900/703	650	720
	Magnesium (mg)	280/219	210	230
	Chloride (mg)	800/625	1250	1250
	Vitamin A (mcg RE)	1020/797	580	820
	Vitamin D (mcg)	17/13	9.3	7
	Vitamin E (mg α-TE)	16/13	19	25
	Vitamin K (mcg)	66/52	100	53
	Vitamin C (mg)	130/102	110	150
	Thiamine (mg)	1.9/1.5	1.5	1.5
	Riboflavin (mg)	2/1.6	1.8	1.6
	Niacin (mg NE)	23/18	17	18
	Vitamin B6 (mg)	2.1/1.6	2.1	1.7
	Vitamin B12 (mcg)	2.6/2.0	3	5
	Folic Acid (mcg)	330/258	250	380
	Pantothenic Acid (mg)	6.6/5.2	7.5	5.3
	Biotin (mcg)	50/39	40	40
**Trace Elements**				
	Iron (mg)	20/15.5	13	16
	Zinc (mg)	15/11.7	12	12
	Manganese (mg)	4.1/3.2	3.5	3.3
	Copper (mcg)	2250/1758	1400	1800
	Iodine (mcg)	170/133	110	130
	Molybdenum (mcg)	130/102	100	100
	Selenium (mcg)	71/56	50	75
	Chromium (mcg)	83/65	85	120
Osmolality (mOsmol/kg H_2_ O)		360	450	360

^a^Percentage of total calories; E: energy.

##### Scientific Measures

Many of the quantitative data measures will be collected within the first 48 hours post randomization including glycemic variability [41], tolerance of enteral nutrition and ability to meet nutritional requirements if there were no clinical contraindications [42]. Glycemic variability will be measured using routinely collected glucometer blood glucose readings which are taken between hourly and 4 hourly, depending on previous blood glucose and insulin rate. The mean and standard deviation of these values will be utilized to calculate the coefficient of variation which forms a surrogate marker of variability [43]. Tolerance of prescribed nutrition will be measured through establishing the incidence of diarrhea commencing post-randomization, the collection of gastric residual volumes [44,45] and potential subsequent use of prokinetics as well as ability to meet recommended goal rates of nutrition in the absence of any clinical contraindication. Goal rates are calculated based on protein requirements of 1.2-1.5g/kg body weight (BW) or adjusted ideal body weight (AIBW) and 25-30kcal/kg BW/AIBW [46]. Adjusted ideal body weight is to be used in the instance a patient has a body mass index greater than 25kg/m^2^.

##### Process Measures Used to Assess Feasibility

Suitable patients, based on the inclusion and exclusion criteria, will be identified by clinical staff and subsequently eligibility and consent verified by the trial research staff. The eligibility criteria used in this study methodology will be assessed for sufficiency to ensure patients are appropriately screened, consented and recruited. Furthermore, data obtained from this study will be used to determine whether a pre-defined period of time expected on nutrition support is required as a component of the inclusion criteria. This will be assessed by the proportion of patients reaching the 48-hour mark on nutrition support. Recruitment rates will be determined by the number of eligible patients who consent in their own right or consent has been obtained from their legally authorized representative. Refusal of consent at either of these points will be recorded with reasons if provided. Based on predictive modelling of patient numbers for Mater Health ICUs to date it is expected that patients will be recruited over a two-and-a-half-year period. This can be extended for a further 6 months dependent upon recruitment rates. The pilot study intends to recruit a minimum of 54 patients.

#### Tertiary Outcome Measures

Length of ICU and hospital stay data as well as mortality outcomes will be investigated at 28 days through a follow up phone call in the instance a patient has been discharged from the hospital, or by access to medical records in the event of death before hospital discharge. Within scripted questions, data related to weight, weight history, diet and functional capacity pre and post ICU admission, will be collected, based on adaption from a validated malnutrition assessment tool (Patient-Generated Subjective Global Assessment) [47]. Blood glucose control including insulin/oral hypoglycemic use pre and post ICU admission will also be explored. The planned sub-study aims to analyze blood and urine samples to establish differences in acute and chronic inflammatory markers, cortisol, oxidative stress and anti-oxidant capacity between baseline and 48 hours later while on differing nutritional products [48-53]. Blood samples will be retrieved through existing arterial lines, centrifuged within 45 minutes and stored at negative eighty degrees Celsius until batch analysis. Urine samples will be taken and aliquots stored under the same conditions.

### Statistical Considerations and Data Analysis

#### Sample Size

There is a minimum target recruitment of 54 patients for this pilot feasibility trial (refer to Figure 2). Two arms of this study will require nineteen patients each to detect a statistically significant difference (alpha 0.05) with a power of 80% based on a median difference of 21.5 units of insulin per day and a common standard deviation of 22.5 units. This has been modeled after the enteral formula study by Mesejo, et al. (2003). For the third arm, a sample size of 10 patients will be randomized for the nested cohort study investigating relevant biomarkers. A 10% buffer of two patients per arm, in the instance of retracted consent or earlier than expected cessation of nutrition, has been accounted for in the target sample size of 54 patients with 21 patients in the primary study (two arms) and 12 in the third arm forming part of the nested cohort study i.e. 2 additional patients per arm.

#### Data Analysis Plan

The analysis will be performed using R commander software or equivalent. Descriptive statistics (frequency, means and standard deviations, medians, interquartile ranges and full ranges) will be calculated for relevant demographic and baseline variables as well as for trial endpoints. Linear, logistic and time-to-event analyses will be performed using relevant data, returning point estimates of effect with associated 95% confidence intervals. Cross sectional analyses in cohort study data with equal follow-up time per subject will be analyzed with linear (for continuous outcomes) or logistic models (for categorical outcomes). Univariable time to event analyses will use Kaplan-Meier curves and differences will be tested using log rank tests.

Adjusted time-to-event analyses will use Cox proportional hazards models, with the assumed proportionality of the hazard subject to verification. Analyses using data collected over time within individual patients will be modeled using methods that account for patient-level clustering (generalized estimating equation methods or mixed linear or logistic models). In the event of non-negligible proportions of missing data, sensitivity analyses will present both the results of complete case analyses and multiple imputation analyses. Linear regression analyses will be used to analyze results from the nested cohort study to determine the contribution of AGE intake (total feed delivered accounting for formula content), AGE output (urine output accounting for AGE level in the urine) and insulin dose (area under the curve) on sRAGE levels.

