### Study Objectives

The primary aim of this study is to determine whether the administration of a DSF reduces insulin administered to critically ill patients with hyperglycemia during enteral nutrition compared to a standard liquid nutritional formula over a 48-hour period. Secondary outcomes will also be explored including the feasibility of study processes to build toward a future multi-site RCT.

A nested cohort study will also be conducted to facilitate a greater understanding of the underlying pathophysiology in critically ill patients. It will specifically seek to determine whether altered CHO and advanced glycation end product (AGE) intake, is associated with oxidative stress markers in addition to acute and chronic inflammatory biomarkers.

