### Study Design

Following consent participants will be randomized to either control, which is the unit’s standard nutritional formula, Nutrison Protein Plus Multifibre (Nutricia), or the intervention, which is a low CHO, low glycemic index DSF, Glucerna Select (Abbott Nutrition). For the purpose of the nested cohort study, a second intervention arm using a different low glycemic index DSF will be used [Diason (Nutricia)]. Refer to Table 1 for a complete nutritional breakdown of these products. Varying advanced glycation end-product content of the differing DSF necessitates the third arm as part of this study. Randomization to the second intervention arm will be ceased once a complete set of blood and urine samples are available for a minimum of 10 participants in each group, with 12 patients set as the target recruitment to account for retracted/declined consent, incomplete sample sets in the instances of extubation or discharge to the ward prior to retrieval. These samples will be collected from all patients at randomization and 48 hours later. Once this has been achieved, randomization will revert to control [Nutrison Protein Plus Multifibre (Nutricia)] and intervention [Glucerna Select (Abbott Nutrition)] groups only. Collection of urine and blood samples for biomarker assay will also be discontinued at this point.

Each envelope will include detailed instructions for clinical staff regarding nutritional formula type labeled as Feed A, B or C and a protocolized delivery rate. The rate has been determined to minimize difference in protein provision in an effort to mitigate confounding factors based on studies identifying the protein as having a protective effect [2]. Once group allocation has occurred, participants will remain on their specified study formula as long as tube feeding continues in ICU or at the discretion of the treating clinician. If the participant were to withdraw from the study, clinical care would revert to usual practice such that the formula will be changed over to what would have otherwise been used had the trial not taken place (Nutrison Protein Plus® or Diason® - Nutricia). Due to the pragmatic nature of this study, all other aspects of care will occur as per routine clinical practice. That is, rates of feeding and treatment of intolerance to enteral nutrition will be as per the unit’s standardized enteral feeding protocol.

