### Outcome Measures

#### Primary Outcome Measures

The primary outcome of this study is the difference in total amount of insulin per 24 hours administered to patients following commencement of the study formula until the 48-hour time period [7]. Pre-study insulin use will also be recorded from the patient charts for the 12 hours preceding randomization.

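### The nested-cohort regression omits delivered carbohydrate, which the aim names, so its AGE coefficient may carry a carbohydrate effect of unknown size

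*Protocol article*

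**What the plan says.** Study Objectives gives the nested cohort two exposures: it will "determine whether altered CHO and advanced glycation end product (AGE) intake, is associated with oxidative stress markers", and with inflammatory biomarkers as well. Tertiary Outcome Measures says the samples are to "establish differences in acute and chronic inflammatory markers, cortisol, oxidative stress and anti-oxidant capacity between baseline and 48 hours later", on the different products.

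Data Analysis Plan then lists the terms of one regression for the nested cohort. Linear regression is to "determine the contribution of AGE intake (total feed delivered accounting for formula content), AGE output (urine output accounting for AGE level in the urine"). The third and last predictor listed is insulin dose, taken as an area under the curve, and the outcome is the sRAGE level. The list has no term for delivered CHO and none for baseline sRAGE. It does not say whether the outcome is the 48-hour value or a change.

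Three other statements bear on this. Study Design says samples are taken at randomization and 48 hours later, and that the third arm exists because the two diabetes-specific formulae differ in AGE content. On delivery it says "The rate has been determined to minimize difference in protein provision". Primary Outcome Measures makes insulin the trial's main outcome: the "difference in total amount of insulin per 24 hours administered to patients following commencement of the study formula until the 48-hour time period".

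**The concern.** The first exposure named in the aim is missing from the model. Because the predictors are listed one by one, this is a mismatch between two statements in the article and not a detail left open.

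The omission could also affect the exposure that is in the model. AGE intake is defined as feed delivered times formula content, and CHO intake has the same form. If CHO intake affects sRAGE and differs between patients along with AGE intake, a model without CHO credits some of that effect to AGE. A reader could then take a CHO effect for an AGE effect, or miss an AGE effect that a CHO effect in the other direction masks.

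**Working it through.** **Figures in the plan.** The article gives no calculation for the nested regression. Its one derived sample size, 19 per arm for the primary comparison, does reproduce: with a difference of 21.5 and an SD of 22.5, a t-test (two-sided 5% assumed) has power 0.795 at 18 per arm and 0.817 at 19. Nothing below depends on it.

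**Step 1: structure.** For a patient receiving volume V of formula k, CHO intake = V × c_k and AGE intake = V × a_k. Within an arm both are V times a constant, so their correlation is exactly 1. Only differences between formulae in the ratio a_k/c_k can separate them, and only if both are in the model.

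**Step 2: how far CHO differs.** Inputs are from Table 1, per 1000 mL.

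| | Control | Glucerna Select | Diason |
|---|---|---|---|
| CHO (g) | 141 | 75 | 113 |
| Protein (g) | 63 | 50 | 43 |
| Energy (kJ) | 5350 | 4170 | 4350 |
| CHO (g) at 63 g protein | 141 | 75 × 63/50 = 94.5 | 113 × 63/43 = 165.6 |

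Diason against Glucerna Select, the pair whose AGE difference justifies the third arm:
- equal volume: 113/75 = 1.51, or +51%
- equal protein: 165.6/94.5 = 1.75, or +75%
- equal energy: (113/4350)/(75/4170) = 1.44, or +44%

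Study Design aims to minimize protein differences, while Scientific Measures bases goal rates on protein and energy. The delivered contrast is therefore not fixed exactly, but it is large on every basis.

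**Step 3: what omission does.** If the true coefficients are β_A for AGE intake and β_C for CHO intake, the model without CHO estimates β_A + β_C × δ. Here δ is the coefficient of AGE intake when CHO intake is regressed on the listed predictors. The article gives neither a_k nor β_C, so the sign and size of β_C × δ cannot be worked out from it.

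**Step 4: range under assumptions.** Three arms of 10 were simulated with Table 1 CHO and protein contents. The assumptions were:
- protein-matched or equal volumes, with a volume CV of 10% or 30%
- ten patterns of relative AGE content, giving 40 scenarios in all
- sRAGE rising by 0.5 residual SD per SD of CHO, with no AGE effect
- insulin dependent on CHO, and AGE output dependent on AGE intake

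| Result over the 40 scenarios | Range |
|---|---|
| AGE–CHO correlation | −0.82 to +0.99 |
| Mean AGE coefficient, listed model (true value 0) | −0.37 to +0.50 |
| AGE declared significant at 5%, listed model | 4% to 55% |
| Same, with delivered CHO added | 3% to 6% |

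**Step 5: price of adding CHO.** Variance inflation from the AGE–CHO correlation, 1/(1 − r²), was 1.0 to 4.7 in 28 scenarios. In the 12 where Glucerna Select was given clearly less AGE than both other formulae, so that AGE content tracks CHO content, it was 6.3 to 38.5. Intervals there are √6.3 = 2.5 to √38.5 = 6.2 times as wide. The sub-study has 3 × 10 = 30 to 3 × 12 = 36 patients.

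**Step 6: baseline sRAGE.** Adjusting for a baseline value with correlation r to the 48-hour value cuts residual variance by r². For an assumed r of 0.5 to 0.7 that is 25% to 49%. This is a gain in precision; leaving baseline out does not create confounding with CHO.

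**The case against.** The other side has good points.

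- **The bias is not shown.** It needs AGE contents and a CHO effect on sRAGE, and the article supplies neither. In some assumed patterns the correlation, and so the bias, was near zero. This stands: the AGE coefficient may carry a CHO effect, and one cannot say that it will.
- **The regression is not the whole nested plan.** A reader might infer that the three-arm contrast goes unused or that baseline is ignored. The article does not support that. Tertiary Outcome Measures plans baseline-to-48-hour comparisons across products, and Data Analysis Plan provides linear models for cohort data and clustered models for repeated data. A comparison of products still does not replace the CHO term, since each formula bundles its AGE and CHO.
- **AGE output and insulin are there on purpose.** The sentence asks for the contribution of each, and Study Objectives speaks of association. A reader might call their inclusion an error, but that presumes a total-effect question the article does not pose. What stands is narrower: both arise after randomization, and insulin is the outcome the formula is expected to change. The AGE coefficient given both is not the total effect of intake and should not be read as one.
- **A baseline covariate may sit in the full plan.** That is possible, so its absence is no error in itself. It is worth naming because the sample is taken anyway and the group is small.
- **Adding CHO may leave little information.** Step 5 confirms this for some patterns. A wide interval then shows what the design can separate, which a model without CHO conceals.

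**Conclusion.** The aim and the listed regression do not match: CHO intake is named in one and absent from the other, so the regression cannot address the CHO half of the aim. This follows from the text alone.

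That the AGE coefficient may also carry a CHO effect follows from the shared delivered volume and from CHO differences of 44% to 75% between the two diabetes-specific formulae. Its size and direction are not determined. The 4% to 55% range rests on assumed AGE contents, volume variation and CHO effect, and shows only that the problem can be anything from negligible to serious.

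The tempting conclusion that the sub-study cannot answer its own question goes too far. The third arm gives some ability to separate AGE from CHO once CHO is in the model, and product comparisons over time are provided for. The matter is confined to an exploratory nested cohort; the primary insulin analysis is unaffected.

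**What to change.** In Data Analysis Plan, define the outcome of the nested regression as 48-hour sRAGE, and add delivered CHO in grams (delivered volume × Table 1 content) and baseline sRAGE to AGE intake, AGE output and insulin dose. As a secondary display, report the model with and without AGE output and insulin, noting that the AGE coefficient conditional on them is not the total effect of intake. Label the analysis exploratory, since it has five predictors in about 30 to 36 patients.

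The change is to wording only: delivered feed is already needed for AGE intake, CHO content is in Table 1, and a blood sample is taken at randomization. The price is wider intervals for AGE, possibly much wider if AGE content follows CHO content across the formulae. Reporting the AGE–CHO intake correlation beside the results would let readers see which case applies.

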**Figure 2 figure2:**
[figure not shown]
Study flow diagram of recruitment, randomization and study conduct. Once consented patients will be randomized on a 1:1:1 ratio until there are 12 patients who have complete blood and urine sample sets from each group to form the biomarker sub-study. Thereafter the study will proceed with two arms as indicated. Finalized patient numbers have not been provided as this is a feasibility study.

## Results

Recruitment to this study commenced in February 2015 and has an estimated completion date for data collection by May 2018. Results are expected to be available in late 2018.

## Discussion

### Expected Outcomes and Potential Significance

The findings of this feasibility study will be used to refine the design of a larger multi-center trial identifying protocol strengths and limitations and importantly returning preliminary study effect estimates for sample size estimation. A more detailed budget will also be established using data from this initial study.

The pragmatic approach of negligible alterations to the pre-existing ICU policies and procedures regarding glucose management is intentional, aiming for this study to proceed with minimal disruption to standard ICU clinical work routines. If successful, a subsequent larger multi-center trial derived from the present proposed pilot study may clarify the efficacy of an intervention altering the composition of enteral nutrition in ICU patients as a standalone therapy for dysregulated glucose management in ICU patients.

### Conclusion

Treatment of hyperglycemia, predominantly involving insulin therapy, remains controversial in the critically ill. While there is evidence to indicate diabetes specific enteral nutrition formulae are beneficial in reducing blood glucose levels in general patients with diabetes, at both a ward and community level, limited evidence supports this practice in the intensive care setting. At present, modification of the composition of enteral nutrition is rarely considered to be an efficacious mode of therapy for glucose control despite its significant contribution to total carbohydrate intake. This pilot study intends to investigate the feasibility and efficacy of diabetic specific nutrition formulations as an additional therapeutic measure in glucose management in the ICU.

## Abbreviations

AIBW: adjusted ideal body weight
AGE: advanced glycation end product
APACHE: acute physiology, age and chronic health evaluation
BW: body weight
CHO: carbohydrate
DSF: diabetes-specific formula
HREC: Human Research Ethics Committee
ICU: intensive care unit
RCT: randomized controlled trial
